**Fig. 2 Fig2:**
[figure not shown]
Participant's timetable . SCC stainless steel crown, ZC zirconia crown

We will blind the statistician supervising the analyses because it is feasible and it reduces the risk of certain biases (e.g., detection bias). It is not possible, however, to blind patients, operators, or outcome examiners because each crown treatment (ZC and SSC) has its own specific color.

### Randomization

Each tooth of the pair (two contralateral PM in the same arch) in the patient will receive one of the two treatments. PMs will first be allocated to SSCs, which correspond to the gold standard treatment; 1 to 2 weeks later, the contralateral PM of the same pair will be restored by ZCs (e.g., if an SSC is assigned on the right PM, the left tooth of the pair will be treated with a ZC). This randomization method focusing first on SSCs has the advantage of being without consequence for one of the secondary outcomes (parental and child satisfaction). The randomization will be performed using a computerized and centralized system at the Nice University Hospital (CHUN) via a specific website (INCLUSIO, https://inclusio.chu-nice.fr) after inclusion of the subject. The sequence of randomization will be stratified by center and dental arch.

### Study population

The participants and dental eligibility criteria are described in Table 1. Dental exclusion criteria have been chosen to reduce failure that is independent of the treatment studied. No special concomitant dental care or intervention is prohibited in children after inclusion in the trial, except that concerning the included teeth.

**Table 1 Tab1:** Eligibility criteria

Inclusion criteria	
• Child aged 4–13 years old in good general health (American Society of Anesthesiologists (ASA) class I or II)	
• Child covered under health insurance of their parent(s)	
• Child and parent(s)/legal guardians speak French	
• Consent of parents/legal guardians and child	
• Child cooperative in the vigilant or sedated state (Venham score of 0, 1, or 2) [12]	
• Child with at least two primary molars (PMs) of the same type (first or second PMs) contralateral (fractional mouth) meeting the following criteria:	
– the two PMs of the pair (54–55, 64–65, 74–75 or 84–85) are affected by a cavitated carious lesion or a hypoplastic defect on at least two surfaces.	
– both PMs of the pair may or may not have a pulpotomy prior to the placement of the preformed pediatric crowns	
– each PM of the pair must have an antagonist tooth	
General exclusion criteria	
• Noncompliant child for dental care in the vigilant state or under conscious sedation, who must therefore be treated under general anesthesia	
• Child allergic to local anesthesia, chromium, or nickel	
Dental exclusion criteria	
• Severely decayed PM prohibiting the retention and the sealing of the restoration	
• PM with spontaneous pain	
• PM with exposed cement or with evidence of swelling in the surrounding tissues	
• PM in infraclusion	
• PM whose radiographic examination reveals a widening of the desmodontal space, the presence of radiolucent image on the root furcation and/or apices, internal or external resorption	
• PM whose physiologic exfoliation will appear within 24 months or PM with a root resorption of more than a third of the radicular length	

### Recruitment procedures

Participants will be recruited in nine Departments of Pediatric Dentistry in the university hospitals of Bordeaux, Lille, Nancy, Nantes, Nice, Paris Bretonneaux, Paris Louis Morrier, Strasbourg, and Toulouse. Each center will recruit an average of 12 children (inclusion from September 2018 to February 2020). The participant's timetable is shown in Fig. 2 and the flow chart of the study is shown in Fig. 3. To encourage recruitment in order to reach the target sample size in the 18-month period, the principal investigator ([name]) will send a text message of encouragement, with general center recruitments mentioned after each inclusion.

**Fig. 3 Fig3:**
[figure not shown]
Study flow chart. ASA American Society of Anesthesiologists, P parent, PPC preformed pediatric crown, SCC stainless steel crown, ZC zirconia crown

At the first visit, eligibility criteria (Table 1) will be verified by the operator in each center after the clinical and radiographic examination. Potential eligible participants and their legal guardians will receive information about the study. The inclusion will then be formalized after legal guardians and the child sign the informed consent forms.

### Intervention

At the second visit, the randomization will take place. The center operator will then perform the restoration with an SSC (ESPE; 3M, Paris France). The tooth is anesthetized, demineralized dentine will be removed and, if a pulpotomy is needed, the rubber dam must be placed on the PM to perform the treatment (pulpotomy with IRM; Dentsply Sirona, Charlotte, NC, USA) and the subsequent restoration is with high-viscosity glass ionomer cement (GIC) (Equia Forte; GC, Leuven, Belgium). The tooth will be prepared by occlusal and proximal reduction; a SCC will be tried and adjusted to fit the tooth. Occlusion is checked, and the SSC will be sealed with a GIC (CVI Fuji Plus; GC).

At the third visit (1 to 2 weeks later), the operator will undertake restoration of the other PM with a ZC (EZCrown; Sprig Oral Health Technologies). After anesthesia and excavation of demineralized dentine, a pulpotomy will be performed only if it was indicated on both PMs of the pair (pulpotomy after rubber dam placement with IRM; Dentsply Sirona). After the subsequent restoration with high-viscosity GIC (Equia Forte; GC), the PM will be prepared following the manufacturer’s guidelines by occlusal, peripheral, and infra-gingival reduction. The ZC will be tried and occlusion will be checked, and the ZC will be sealed with a GIC (CVI Fuji Plus; GC).

The operators (one per center) have followed a course organized by [name] (using videos) and received training on Typodont models on how to prepare teeth for ZCs.

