### Study outcomes

The primary outcome is the success of the treatment. Success will be defined by the absence of major failure. A composite measure of signs and symptoms leading to diagnosis of irreversible pulpitis or periradicular periodontitis will be used to define major failure. This composite measure includes one or more of the following: pain, pulp infection, dental abscess, and periradicular pathology visible on radiograph [3].

The secondary outcomes are parental and child satisfaction (size, form, and color), retention and fracture of the PPC (two dichotomized variables, yes/no), the gingival state near the PPC using the indices Löe and Silness to record plaque index (PI), gingival index (GI) and depth of the pocket (DI) on the crowned tooth and the two adjacent teeth [8].

Parental and child satisfaction will be evaluated on a five-point Likert scale [11]. The DI will be assessed by soft periodontal probing on the sulcus mesial, distal, vestibular and lingual areas of the teeth. Finally, the wear of the antagonist tooth will be recorded (0: absence of wear; 1: wear on only the cusp point; and 2: wear at least at the cusps) [9, 10]. The presence or absence of a restoration with a dental material of the antagonist tooth will be also recorded.

Primary and secondary outcomes will be assessed clinically and radiographically by independent evaluators, one per center, at different periods during the study (postintervention and every 6 months during a total follow-up of 2 years). To prevent information bias, the evaluators will not be the operators who applied the treatment.

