### Assessment and data collection

#### Baseline visit

At the first visit, before treatment commences, participant characteristics (e.g., age and sex), the numbers of teeth included (54–55, 64–65, 74–75, 84–85), the number of surfaces affected by the carious lesion or the hypoplastic defect, and the pulpotomies indicated in both teeth, will be recorded by the nine operators (one per center).

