The choice of assessment criteria for the primary outcome is based on the systematic review of Innes et al. [3]. Using the same composite criteria will allow this RCT to be included in a future meta-analysis to compare different PPCs; their choice is more appropriate than the US Public Health Service criteria that is used more for the assessment of dental fillings. The success rate of a restoration can be related to the survey rate (presence in the mouth) of the tooth after 2 years of follow-up. This has the advantage of being longer than the 6 or 12 months of follow-up used in other studies focusing on PPCs [6, 7]. Other aspects of the criteria are also important and guide the choice of the criteria for the secondary outcome. The success of a restoration also includes its retention and integrity, the health of surrounding structures, and the satisfaction of both patients and parents with the restoration.

The clinical procedure is carried out under optimal conditions. One of the main advantages is that, if a pulpotomy must be done on the two PMs of the tooth pair, it has to be done under rubber dam isolation. Furthermore, the two PMs must present similar decay in depth, but this is often the case in children.

With sustained poor oral health in most developed communities [25], and greater importance being given to esthetic factors, the results of the present RCT will inform clinicians regarding the selection of clinical treatment options for severe dental decay which affect most children. The results will help them explain to the parents the advantages and disadvantages of the two possible solutions. The results will allow for advancement in the recommendations, and will be beneficial for the patient, the practitioner, and the public healthcare system.

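### The pulpotomy rule is worded differently for the two crowns: read literally, a zirconia-crown tooth that alone needs a pulpotomy is crowned without one

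*Protocol article*

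**What the plan says.** The Intervention section of the protocol article gives one instruction per visit.

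- **Visit 2, SSC tooth.** After anesthesia and removal of demineralized dentine: "if a pulpotomy is needed, the rubber dam must be placed on the PM to perform the treatment". The other tooth is not mentioned.
- **Visit 3, ZC tooth, 1 to 2 weeks later.** "After anesthesia and excavation of demineralized dentine", the text continues that "a pulpotomy will be performed only if it was indicated on both PMs of the pair".

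Other sections bear on how to read this:

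- Table 1 (Study population): "both PMs of the pair may or may not have a pulpotomy prior to the placement of the preformed pediatric crowns".
- Baseline visit: "the pulpotomies indicated in both teeth, will be recorded by the nine operators", before treatment starts.
- Discussion: "if a pulpotomy must be done on the two PMs of the tooth pair, it has to be done under rubber dam isolation", and "the two PMs must present similar decay in depth, but this is often the case in children".
- Statistical analysis: pulpotomy appears among the tooth-pair descriptors and again as a covariate in the Cox shared-frailty model.
- Study outcomes: "A composite measure of signs and symptoms leading to diagnosis of irreversible pulpitis or periradicular periodontitis will be used to define major failure".

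**The concern.** The two instructions apply at the same procedural step but set different conditions, and the condition follows the crown. A split-mouth comparison relies on the two teeth being handled alike apart from the crown. Here the text makes pulp treatment of the ZC tooth depend on the state of its partner, and does not do so for the SSC tooth.

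An indicated pulpotomy is meant to prevent the events that count as major failure. If it is withheld in one arm only, part of any difference between arms reflects pulp treatment rather than the crown. Randomizing the side does not help, because the rule is attached to the crown and not to the side. Apart from any bias, the literal rule would leave a child without a treatment judged to be needed.

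**Working it through.** **Step 1. Apply the two instructions, as written, to every type of pair.**

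| Pulpotomy needed in | SSC tooth | ZC tooth | Consequence |
|---|---|---|---|
| neither tooth | none | none | arms alike |
| both teeth | done | done | arms alike |
| SSC tooth only | done | none, none needed | each tooth treated as needed |
| ZC tooth only | none, none needed | not done, although needed | indicated treatment withheld, ZC only |

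Only the last row is a problem. An SSC tooth never meets the equivalent situation.

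**Step 2. Can the last row occur under the plan?** Table 1 permits pulpotomy but does not make the same indication in both teeth a criterion. Similar depth of decay is stated in the Discussion, not among the listed criteria, and is described there as frequent. The Possible problems section itself expects difficulty in finding equivalent lesions. Similar depth at baseline also does not guarantee the same need once each tooth is opened, at separate visits. The row is therefore possible, though probably uncommon.

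**Step 3. Does the covariate repair it?** No. If the pulpotomy covariate records treatment performed, the affected ZC tooth is coded as having none, like a tooth that needed none. If it records the indication, the tooth is grouped with teeth that were indicated and treated. In both cases the excess risk falls on the treatment term.

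**Step 4. Scale.** The plan's own figure first: (1.645 + 1.282)² × 2 × 0.95 × 0.05 / 0.10² = 81.36, against the stated 81 teeth per group. At 95% success this means 81 × 0.05 = 4.05 expected failures per arm, so one extra failure is 1/81 = 1.2 percentage points.

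Let d be the share of discordant pairs and e the excess failure risk when an indicated pulpotomy is withheld. The documents give neither. With side randomized, about half of the discordant pairs have the ZC tooth as the one in need:

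- Shift in ZC success = (d/2) × e.
- One extra expected failure requires 81 × (d/2) × e = 1, so d × e = 2/81 = 2.5%. That is 4 discordant pairs of 81 if e = 50%, 8 if e = 25%, or 20 if e = 10%.
- Assuming d = 2% and e = 10%: 0.01 × 0.10 = 0.1 points, or 0.08 failures.
- Assuming d = 5% and e = 25%: 0.025 × 0.25 = 0.6 points, or 0.5 failures.
- If all pairs are concordant, d = 0 and the shift is zero.

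Much larger inputs give much larger shifts: d = 20% and e = 80% would give 8 points. The similar-depth statement argues for a low d. The exclusion of teeth with spontaneous pain, swelling or radiolucency argues for a lower e. These lines show only how the answer depends on the two unknowns; they are not estimates.

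**The case against.** The strongest reply is that this is loose drafting. The past tense in the ZC sentence can be read as pointing back to the indications recorded for both teeth at baseline. Table 1, the list of tooth-pair descriptors and the Discussion all treat pulpotomy as a property of the pair. On that reading the visit 2 wording is shorthand for the same pair-level status, and the arms do not differ. Harm would also need an operator to follow the sentence literally and crown a tooth with a recognized pulp indication. A journal article may leave unexpected findings at excavation to the full protocol.

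Much of this stands. Matched pairs were probably intended, and nothing suggests a deliberate difference between arms. It does not remove the point, for three reasons. The intention is nowhere written as a rule for both teeth. Tying the condition to the baseline record does not cover need found only at excavation. And this is not an omitted detail: the article states an operative instruction for each arm, and the instructions differ.

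A reader might go further and infer that the wording costs the trial power. Under the protocol's formula, one extra ZC failure would lower power from 89.9% to 78.2%. The documents do not support that inference. It presupposes d × e of about 2.5%, and neither factor is given. The figures are also one-sided for independent proportions, whereas the trial claims equivalence: two one-sided tests at the same inputs give 79.8% and 71.0%. The planned primary analysis is in any case a hazard ratio from a frailty model.

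**Conclusion.** The concern holds as a defect of wording with a possible one-sided consequence. The Intervention section gives different pulpotomy rules by crown. Read literally, the ZC rule withholds an indicated pulpotomy from a ZC tooth that alone needs one. Any resulting bias is against ZC and lies on the direct path to the primary outcome.

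The effect is limited to pairs of that kind. Its size is unknown and probably small, and it vanishes if all pairs are concordant both at baseline and at excavation. It also rests on operators following the sentence as written. It would be wrong to conclude that the trial is biased by a known amount or has lost power. The case for acting is that the rule touches the primary outcome and the child's care, and that correcting it costs almost nothing.

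**What to change.** In the Intervention section, replace the ZC condition with one rule stated for both teeth at visits 2 and 3: a pulpotomy is performed when clinically indicated in that tooth, including need discovered during excavation, whichever crown the tooth is to receive.

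This costs one sentence, processed as an amendment by the route given under Ethical consideration. It needs no extra visits or staff and no change in sample size.

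Two additions are optional and not needed for the fix:

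- Showing the primary result also in pairs concordant on the baseline indication, which is already recorded. It adds little once the rule is the same for both teeth.
- Adding to Table 1 that both teeth share the same baseline indication. This would lose some eligible pairs in a trial that already expects recruitment difficulty, and would still need the per-tooth rule for need found at excavation.

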### Study outcomes

The primary outcome is the success of the treatment. Success will be defined by the absence of major failure. A composite measure of signs and symptoms leading to diagnosis of irreversible pulpitis or periradicular periodontitis will be used to define major failure. This composite measure includes one or more of the following: pain, pulp infection, dental abscess, and periradicular pathology visible on radiograph [3].

The secondary outcomes are parental and child satisfaction (size, form, and color), retention and fracture of the PPC (two dichotomized variables, yes/no), the gingival state near the PPC using the indices Löe and Silness to record plaque index (PI), gingival index (GI) and depth of the pocket (DI) on the crowned tooth and the two adjacent teeth [8].

Parental and child satisfaction will be evaluated on a five-point Likert scale [11]. The DI will be assessed by soft periodontal probing on the sulcus mesial, distal, vestibular and lingual areas of the teeth. Finally, the wear of the antagonist tooth will be recorded (0: absence of wear; 1: wear on only the cusp point; and 2: wear at least at the cusps) [9, 10]. The presence or absence of a restoration with a dental material of the antagonist tooth will be also recorded.

Primary and secondary outcomes will be assessed clinically and radiographically by independent evaluators, one per center, at different periods during the study (postintervention and every 6 months during a total follow-up of 2 years). To prevent information bias, the evaluators will not be the operators who applied the treatment.

### Assessment and data collection

#### Baseline visit

At the first visit, before treatment commences, participant characteristics (e.g., age and sex), the numbers of teeth included (54–55, 64–65, 74–75, 84–85), the number of surfaces affected by the carious lesion or the hypoplastic defect, and the pulpotomies indicated in both teeth, will be recorded by the nine operators (one per center).

#### Follow-up visits

After 6, 12, 18 and 24 months of follow-up, the primary (success criteria) and secondary outcomes (see Study outcomes section above) will be assessed by the nine evaluators (one per center and not the operator in each center).

To improve internal validity, evaluators (one per center) will be trained and calibrated on how to assess the study outcomes by means of repeated exercises on the Socrative website (https://socrative.com/) with clinical cases presented in a random way using the model of e-calib [13]. These exercises as prepared by Dr [name] (Department of Pediatric Dentistry, Faculty of Dentistry, Nice, France), [name], EA, and [name] will allow the evaluation of the inter- and intra-evaluator agreement (Kappa coefficients).

### Data management

The baseline data, follow-up trial data, and adverse events will be recorded by operators and evaluators on case report forms (CRFs). Data will be kept anonymous. Patients will be identified by their inclusion data; only the number of the patient, number of the center, and the initial letter of their first and last name will be registered on the CRF.

### Sample size

Table 2 shows the sample size calculation for success rates ranging from 95% to 97%, alpha equal to 5%, with 90% power and an equivalence margin between the study groups of 10%. This table illustrates that the effective sample size of 81 teeth per treatment group will provide a power of 90% to assess effectiveness equivalence between the treatment groups. These rates were based on the systematic review of Innes et al. [3]. This calculation was based on the formula (Z _0.95_ + Z _0.90_)^2^ [Ps (1 – Ps) + Pn (1 – Pn)] / (Ps – Pn – D)^2^ (see http://people.ucalgary.ca/~patten/blackwelder.html) [14].

**Table 2 Tab2:** Sample size calculation

Rate	Teeth	Total required
80	274	548
85	218	438
90	154	308
95	81	162
97	49	98

Note: Rate of the outcome for the study groups, power = 90%, alpha = 5%, equivalence margin = 10%

Additionally, when we consider a hazard ratio (HR) = 1, moderate intraclass correlation (ICC) = 0.05, the percentage of teeth in each study group of 50%, the probability of observing an event of 90%, and two one-sided test (TOST) Zα = 1.64, this sample size of 81 teeth provides 80% power to test the equivalence between the study groups for margins ranging from 0.7 to 0.9. This sample size was calculated as described in [15].

Furthermore, assuming a dropout around 20%, the total sample size necessary will be 101 children. This dropout value was based on the experience of the research team from previous RCTs conducted in France [16]. This sample size is higher than those of past RCTs assessing the effectiveness of esthetic PPCs, which included 11 to 60 teeth per treatment group [6, 7].

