## Methods

### Trial design and blindness

In this multicenter split-mouth RCT, a PM and its contralateral tooth in the same arch will be randomly assigned to a specific crown treatment group, ZC or SSC (Fig. 2). We plan to screen 101 individuals to successfully recruit 81 patients (see Sample size section below). We decided to use the split-mouth design because each subject forms its own control, adjusting for potential confounders.

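### The stated 90% equivalence power of 81 teeth per group comes from a one-sided, large-sample formula for independent groups; 81 pairs tested against both bounds do not deliver it at 95% success and low within-child correlation

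*Protocol article*

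**What the plan says.** The Sample size section sets "alpha equal to 5%, with 90% power and an equivalence margin between the study groups of 10" per cent and gives the method: "This calculation was based on the formula (Z _0.95_ + Z _0.90_)^2", multiplied by the sum of the two binomial variances and divided by the squared distance to the margin. The 95% row of Table 2 gives 81 teeth per group, and the text concludes that "the effective sample size of 81 teeth per treatment group will provide a power of 90% to assess effectiveness equivalence between the treatment groups". Allowing for 20% dropout turns 81 into 101 children.

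A second calculation in the same section concerns a hazard ratio. It uses two one-sided tests and "moderate intraclass correlation (ICC) = 0.05", and claims 80% power for hazard-ratio margins of 0.7 to 0.9.

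The section on trial design and blindness makes the comparison a paired one: "a PM and its contralateral tooth in the same arch will be randomly assigned to a specific crown treatment group, ZC or SSC". It justifies this because "each subject forms its own control, adjusting for potential confounders". The Statistical analysis section plans a Cox model with a shared frailty for the child, reported as a hazard ratio with a 95% confidence interval.

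**The concern.** The bracket in the formula is the variance of a difference between two unrelated groups. It has no term for the correlation between two teeth of one child, although the design rests on that pairing. The two normal quantiles in the formula are those of a single one-sided test, while the claim is about equivalence, which needs both bounds. And the formula is a large-sample one, applied where about four failures per group are expected (81 × 0.05 = 4.05).

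The figure matters because 81 fixes recruitment. If the true power for equivalence is well below 90%, an inconclusive result is more likely than the protocol tells its readers. If the eventual interval for the 10-point difference were a Wald one, equivalence could also be accepted too easily.

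**Working it through.** **Inputs.** From the Sample size section: success 95% in both groups (the row that gives 81), true difference 0, margin D = 0.10, z(0.95) = 1.645, z(0.90) = 1.282. From the trial design section: one tooth per child in each group, so 81 teeth per group are 81 pairs. Assumed, because the document gives no value for the binary outcome: the within-child correlation r, taken from 0 to 0.5.

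**1. The plan's own figure.** n = (1.645 + 1.282)² × (2 × 0.95 × 0.05) / 0.10² = 8.564 × 9.5 = 81.36. The plan prints 81. The other rows of Table 2 reproduce to within one (274.0, 218.4, 154.2, 49.8). Dropout: 81 / 0.8 = 101.25.

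**2. Add the pairing only.** The variance becomes 2 × 0.95 × 0.05 × (1 − r), so n = 81.4 × (1 − r): 77 pairs at r = 0.05, 65 at r = 0.2, 41 at r = 0.5. One-sided power of 81 pairs is Φ(D/SE − 1.645) with SE = √(0.095 × (1 − r)/81).
- r = 0: SE = 0.0342, power 89.9%
- r = 0.05: SE = 0.0334, power 91.2%

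So the missing covariance does not inflate the 90%.

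**3. Add the second bound.** With a true difference of 0, two-bound power is 2Φ(D/SE − 1.645) − 1.
- r = 0: 2 × 0.899 − 1 = 79.8%
- r = 0.05: 2 × 0.912 − 1 = 82.3% (rounded from unrounded values)

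Equivalently, z(0.90) must be replaced by z(0.95): (1.645 + 1.645)² × 9.5 = 102.8 pairs at r = 0, and 97.7 at r = 0.05.

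**4. Check the large-sample approximation.** Expected discordant pairs are 81 × 0.095 × (1 − r): 7.7 at r = 0, 7.3 at r = 0.05, 3.8 at r = 0.5. I enumerated the exact trinomial distribution of the discordant counts (b, c) for 81 pairs and applied two tests at z = 1.645:
- Wald: (b − c)/n ± 1.645 × √(b + c − (b − c)²/n)/n against ±0.10.
- Paired score (Tango): (b − c − nD)/√(n(2q + D(1 − D))), where q is the discordant probability estimated under a difference equal to the margin.

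Error rate at the margin (95% versus 85%, nominal 5%): the Wald test gives 6.1% (r = 0), 6.3% (0.05), 7.2% (0.2) and 7.9% (0.3). The score test stays between 4.1% and 4.6%.

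**5. Power of 81 pairs at 95% success, exact.**

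| r | Wald, one bound | Wald, both | Score, one bound | Score, both |
|---|---|---|---|---|
| 0 | 89.8% | 79.6% | 82.9% | 65.8% |
| 0.05 | 91.0% | 82.0% | 84.2% | 68.3% |
| 0.2 | 94.2% | 88.3% | 88.0% | 75.9% |
| 0.3 | 95.9% | 91.9% | 90.5% | 81.1% |
| 0.5 | 98.5% | 97.0% | 95.3% | 90.7% |

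**6. The upper end of the stated range, 97% success.** Expected discordant pairs at r = 0: 81 × 2 × 0.97 × 0.03 = 4.7. The score test gives 93–94% for one bound and 85–87% for both at r = 0–0.05. The large-sample two-bound figure is higher: SE = √(0.0582/81) = 0.0268, and 2Φ(3.73 − 1.645) − 1 = 96% at r = 0.

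**The case against.** The strongest reply is that the independent-groups formula errs on the safe side. That is correct: pairing lowers the requirement, and on the one-sided Wald reading 81 pairs give 90–91%. A reader might infer from the missing covariance term that the trial is underpowered because it ignores pairing. The numbers say the opposite, and that reading is not part of this point.

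Second, the protocol names neither a score test nor a paired Wald test. The planned analysis is a frailty Cox model, so the 6–8% error rate is not that of the planned analysis, and the one-sided shortfall to 83–84% appears only with a score test. This stands. But the 90% is claimed for a 10-point difference in success rates, and it should be right for that comparison. The second bound alone brings it to about 80–82% at r = 0–0.05, whichever paired test is chosen.

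Third, dependence is not ignored throughout: the hazard-ratio calculation has an ICC of 0.05, and the Cox model clusters by child. A reader might infer that the two calculations contradict each other, or that r must be 0.05. The documents do not support either. That ICC belongs to a clustered time-to-event calculation and is not shown to be the correlation of paired two-year outcomes. Nor does that calculation support the 90%, since it claims 80% on another scale.

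Fourth, the result depends on the success rate. The section speaks of "Table 2 shows the sample size calculation for success rates ranging from 95% to 97" per cent, and at 97% the one-bound score power exceeds 90%. That also stands, although 81 itself is the 95% figure.

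**Conclusion.** The 81 is computed correctly from the printed formula, but the 90% is not the equivalence power of 81 pairs under the assumptions that produced it. At 95% success and r = 0.05, the steps are: 91% with pairing and one bound, 82% with both bounds, and 68% with both bounds and a paired test that keeps its error rate below 5%. The second bound and the few discordant pairs cause the loss; the pairing does not.

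The size rests on the assumed r and success rate. With the score test and both bounds, power at 95% success runs from 66% at r = 0 to 91% at r = 0.5, and at 97% success it is 85–87% at r = 0–0.05. The documents give no value of r for this outcome. A reader might infer that the trial's true power is 66–68%, or that more children must be enrolled. Neither follows: the first is the low-correlation end of a range for a risk-difference test, and the planned Cox analysis has a power of its own that these figures do not measure. What follows is that the 90% statement should be restated.

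**What to change.** Keep recruitment as it is. In the Sample size section:
- Replace the independent-groups formula by a paired calculation that uses both equivalence bounds and a score (Tango) interval.
- State the within-child correlation, or the discordant-pair rate, as an assumption of its own, not taken over from the ICC in the hazard-ratio calculation.
- Restate the power of 81 pairs over r = 0.05 to 0.5 and success 95% to 97%.

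In the Statistical analysis section, add a paired risk difference with a score interval, compared with the 10-point margin, beside the Cox model. The stated power then belongs to an analysis that the trial performs.

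The cost is text and one extra analysis on data already collected. The drawback is that the stated power becomes less favourable over much of the range.

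### The 80% power claimed for hazard-ratio equivalence assumes 90% events, while the same section expects 3–5% major failures; at that rate the power is zero at every stated margin

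*Protocol article*

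**What the plan says.** The Sample size section of the protocol article holds two calculations.

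- The calculation for proportions is described as a "sample size calculation for success rates ranging from 95% to 97" percent, with a 10-point equivalence margin and 90% power. It leads to an "effective sample size of 81 teeth per treatment group".
- The calculation for the hazard ratio is introduced as an addition. Among its inputs is "the probability of observing an event of 90" percent, and it concludes that "this sample size of 81 teeth provides 80% power to test the equivalence between the study groups for margins ranging from 0.7 to 0.9". It does not say whether the margins are hazard ratios or log hazard ratios, nor whether 81 is a total or a number per group.

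Two other sections bear on the point. Study outcomes defines success as the absence of major failure. Statistical analysis assesses equivalence with a multivariable Cox model with shared frailty that reports a hazard ratio and 95% confidence interval, and it codes success as 1 and its absence as 0.

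**The concern.** Power for a hazard ratio depends on the number of events. If the event is major failure, a 90% event probability contradicts an expected success of 95–97% in the preceding paragraph. The hazard-ratio paragraph is the only power statement for the Cox model, which is the analysis named for the equivalence question. A reader is told that this analysis has 80% power. If the trial runs as expected, the model would rest on a handful of failures, and its interval would be too wide to lie inside any of the stated margins.

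**Working it through.** **Inputs, all from the Sample size section.** 81 teeth per group, so 162 in total; "when we consider a hazard ratio (HR) = 1"; "moderate intraclass correlation (ICC) = 0.05"; "the percentage of teeth in each study group of 50" percent; "two one-sided test (TOST) Zα = 1.64"; event probability 90%; expected success 95–97%, so failure 3–5%.

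**Formula.** With D = teeth × event probability and equal allocation, SE(log HR) = 2/√D. At a true hazard ratio of 1, power = 2Φ(δ/SE − 1.645) − 1, set to 0 when negative. Here δ = |ln(margin)| if the margin is a hazard ratio, or the margin itself if it is on the log scale. The document does not show how the ICC enters. I therefore divide D by 1 + 0.05 = 1.05 (a penalty), by 1 − 0.05 = 0.95 (a gain from the within-child contrast), or leave D alone. Using 1.64 for 1.645 moves the results by less than half a percentage point.

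**1. Reproducing the stated 80%.** Take a log-scale margin of 0.7, 81 teeth in total, 90% events and the 1.05 penalty.
- D = 81 × 0.90 / 1.05 = 69.4, SE = 0.240 and δ/SE = 2.916.
- Power = 2Φ(1.271) − 1 = 79.6% (79.8% with 1.64).
- At 0.8 and 0.9 it is about 91% and 96.5%.
- On this reading the limits are exp(±0.7) = 0.50–2.01, widening to exp(±0.9) = 0.41–2.46.

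**2. Same 90%, margins read as hazard ratios.** Here δ = 0.357, 0.223 and 0.105. With 162 teeth, D = 145.8 and SE = 0.166.
- At 0.7, δ/SE = 2.153 and power is 39% (35% with the ICC as a penalty, 43% as a gain).
- At 0.8 and 0.9, δ/SE is 1.347 and 0.636. Both are below 1.645, so power is 0.
- With 81 teeth in total it is 0 at all three margins.

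**3. The plan's own failure rate.** Failures expected in 162 teeth: 162 × 0.05 = 8.1 and 162 × 0.03 = 4.9.

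| Failures | SE | δ/SE, HR 0.7 | δ/SE, log 0.7 | δ/SE, log 0.9 | Power |
|---|---|---|---|---|---|
| 8.1 | 0.703 | 0.508 | 0.996 | 1.281 | 0 |
| 4.9 | 0.907 | 0.393 | 0.772 | 0.992 | 0 |

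- Every ratio is below 1.645, and hazard-ratio margins of 0.8 and 0.9 are stricter still. The ICC does not change this: with the gain, the largest ratio becomes 0.9 × √(8.1/0.95)/2 = 1.31.
- No dropout would not change it either: 202 teeth × 0.05 = 10.1 failures, and 0.9 × √10.1/2 = 1.43.
- Power exceeds zero only when D > (2 × 1.645/δ)². That is about 85 events for a hazard-ratio margin of 0.7, 22 for a log margin of 0.7 and 13.4 for a log margin of 0.9.
- Before any ICC adjustment, 80% power needs about 269, 688 and 3,086 failures for hazard-ratio margins of 0.7, 0.8 and 0.9, or about 70, 54 and 43 for log margins.
- A 90% interval around an estimate of 1 would be exp(±1.645 × 0.703) = 0.31–3.18 with 8.1 failures.

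**4. Success counted as the event.** With 95–97% events, 162 teeth give 153.9–157.1. Read as hazard ratios, a margin of 0.7 has about 39–48% power across the ICC treatments, and 0.8 and 0.9 have none. On the log scale power at 0.7 would be about 82% or more even with 81 teeth, but for a hazard of success.

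**5. Where the 81 comes from.** The formula for proportions gives (1.645 + 1.282)² × 2 × 0.95 × 0.05 / 0.10² = 81.4, in line with the stated 81 per group. The enrolment figure therefore does not depend on the hazard-ratio paragraph. I use this calculation only to show that.

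**The case against.** The strongest reply is that the calculation was carried out correctly. Step 1 matches the listed inputs and the literal tooth count, and power then rises up to 0.9, as a range of margins would suggest. A reader might infer from the hazard-ratio reading in step 2 that the 80% is an arithmetic error that fails on its own inputs. The document does not support that: it leaves the margin scale unstated, and the method reference it cites is not available here. What can be said is that the figure holds on the log scale with 81 as the total, and fails if the margins are hazard ratios. The log-scale reading still conflicts with 81 per group, and it still needs 90% events.

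A second reply is that Statistical analysis codes success as 1, so the 90% may be a rounded or cautious success probability. This may well be its source. It does not rescue the claim, because 90% is not 95–97% and the hazard of success does not measure crown failure. It does show that the coding needs correcting along with the power paragraph.

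A third reply is that the paragraph is supplementary and sets no enrolment number. That is correct and limits the consequence. The paragraph nonetheless remains the only power statement for the Cox analysis.

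**Conclusion.** The point holds as a conflict between inputs. The hazard-ratio power uses a 90% event probability, and the section's own success rates imply 3–5% major failures. With the 5–8 failures expected in 162 teeth, power for equivalence is zero at every stated margin, on either scale and under any of the ICC treatments tried. The planned Cox analysis does not have the 80% power claimed for it.

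This rests on major failure being the event of interest, a true hazard ratio of 1, the standard large-sample variance for a log hazard ratio, and failure rates as the plan expects. It does not establish that the 80% was miscalculated, nor that the sample size for the 10-point difference is undermined.

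**What to change.** 1. In Sample size, withdraw the hazard-ratio power statement. Alternatively, restate it: about 5–8 major failures are expected in 162 teeth, and the trial has no power to show hazard-ratio equivalence at margins of 0.7 to 0.9. If any hazard-ratio margin is kept, give its scale and say whether tooth counts are totals or per group.
2. Rest the equivalence conclusion on the 24-month difference in success, with the 10-point margin that already sizes the trial.
3. In Statistical analysis, make major failure the event in the Cox model and describe the hazard ratio as supportive, so that the two sections agree.

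The cost is a less favourable power statement and a change to the primary analysis text, which is more than rewording and would go through the amendment route described under Ethical consideration. Enrolment and data collection do not change.
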